# Fluconazole in hypercalciuric patients with increased 1,25(OH)_2_D levels: the prospective, randomized, placebo-controlled, double-blind FLUCOLITH trial

**DOI:** 10.1186/s13063-022-06302-z

**Published:** 2022-06-16

**Keywords:** SLC34A1, SLC34A3, CYP24A1, Hypercalciuria, Fluconazole, 1,25(OH)_2_D, Phosphate, Randomized, Controlled, Nephrolithiasis

## Abstract

**Background:**

Hypercalciuria is one of the most frequent metabolic disorders associated with nephrolithiasis and/or nephrocalcinosis possibly leading to chronic kidney disease (CKD) and bone complications in adults. Orphan diseases with different underlying primary pathophysiology share inappropriately increased 1,25(OH)_2_D levels and hypercalciuria, e.g., hypersensitivity to vitamin D and renal phosphate wasting. Their management is challenging, typically based on hyperhydration and dietary advice.

The antifungal azoles are known to inhibit the 1α-hydroxylase and therefore decrease 1,25(OH)_2_D levels; they are commonly used, with well described pharmacokinetic and tolerability data. Fluconazole has been successfully reported to reduce calciuria in patients with *CYP24A1* or *SLC34A3* mutations, with no safety warnings. Thus, based on these case reports, we hypothesize that fluconazole is effective to decrease and normalize calciuria in patients with hypercalciuria and increased 1,25(OH)_2_D levels.

**Methods:**

The FLUCOLITH trial is a prospective, interventional, randomized in parallel groups (1:1), placebo-controlled, double-blind trial. A total of 60 patients (10–60 years) with nephrolithiasis and/or nephrocalcinosis history, hypercalciuria (> 0.1 mmol/kg/day), increased 1,25(OH)_2_D levels (> 150 pmol/L), and 25-OH-D levels >20 nmol/L will be included. Inclusions will be performed only from mid-September to the beginning of February to avoid bias due to sunlight-induced vitamin D synthesis. The primary endpoint will be the proportion of patients with normalization of 24-h calciuria between baseline and 16 weeks, or with a relative decrease of at least 30% of 24-h calciuria in patients who still display at W16 a 24-h hypercalciuria.

**Discussion:**

The current challenge is to propose an efficient treatment to patients with hypercalciuria and increased 1,25(OH)_2_D levels in order to prevent later complications and notably CKD that can ultimately lead to end-stage renal disease. Based on improvement of knowledge in phosphate/calcium metabolism, pathophysiology and genetics, the “off-label” use of fluconazole was recently reported to be useful in hypercalciuric patients with increased 1,25(OH)_2_D levels. Thus, the FLUCOLITH study is a unique opportunity to develop a new indication of a well-known and not expensive drug in orphan renal diseases, the ultimate objective being the secondary prevention of CKD worsening in these patients.

**Trial registration:**

ClinicalTrials.gov NCT04495608. Registered on July 23, 2020.

**Supplementary Information:**

The online version contains supplementary material available at 10.1186/s13063-022-06302-z.

## Background

Hypercalciuria is one of the most frequent metabolic disorders associated with nephrolithiasis and/or nephrocalcinosis possibly leading to chronic kidney disease (CKD) and bone complications in adults. Due to the availability of genetic testing and improvement of genetic knowledge, some “idiopathic” cases with a mild phenotype are now explained by mutations in *CYP24A1* (encoding the vitamin D 24-hydroxylase enzyme) or *SLC34A1/SLC34A3* encoding the sodium-phosphate cotransporters Npt2a and Npt2c, respectively, and responsible for phosphate reabsorption in renal proximal tubular cells [1, 2].

Hypercalciuria can be secondary to increased intestinal absorption and/or increased renal distal tubular reabsorption of calcium due to increased active vitamin D, i.e., 1,25(OH)_2_D, levels. The putative mechanisms responsible for high 1,25(OH)_2_D levels in kidney stone formers and nephrocalcinosis have been recently reviewed [3]. Briefly, in physiology, fibroblast growth factor (FGF23) inhibits 1,25(OH)_2_D through at least two direct mechanisms: an inhibition of the 1-α hydroxylase and a stimulation of the 24-hydroxylase, thus leading to decreased 1,25(OH)_2_D levels. In contrast, 1,25(OH)_2_D is stimulated by (absolute or relative) hypocalcemia, (absolute or relative) hypophosphatemia, and parathyroid hormone (PTH). Even though they have a different pathophysiology, some diseases share inappropriate increased 1,25(OH)_2_D levels as a direct or indirect result of the underlying defect [3]. This is the case for example for hypersensitivity to vitamin D (*CYP24A1* mutations, or neonatal severe hypercalcemia without genetic explanation), hypercalciuria with renal phosphate wasting (mutations in the genes encoding Npt2a, Npt2c, and NHERF1), or the exceptional familial tumoral calcinosis (low levels of active or resistance to FGF23) [4]. In patients with mutations in the genes encoding Npt2a or Npt2c, the decreased tubular phosphate reabsorption induces both a “downregulation” of FGF23 (which in turn decreases the inhibition of 1,25(OH)_2_D by FGF23) and a direct stimulation of 1,25(OH)_2_D to increase intestinal phosphate absorption to maintain circulating phosphate levels, even in the absence of overt hypophosphatemia. Thus, these two pathways explain the increased 1,25(OH)_2_D levels observed in these patients. Longitudinal data of patients with *CYP24A1* mutations have also suggested that, in most patients, periods of increased sunlight exposure tended to correlate with decreases in PTH levels and increases in both circulating and urinary calcium [5].

The management of these genetic causes of hypercalciuria usually rely on hyperhydration and dietary advice, notably low-sodium diet with normal calcium intake for age. In case of overt hypophosphatemia and subsequent abnormal bone mineralization, phosphate supplementation may be given to these patients, at least during childhood, similarly to what is done in patients with hypophosphatemic rickets [6]. Other strategies such as hydrochlorothiazide can be proposed, however with an uncertain medical benefit in view of side effects (hypokalemia, asthenia, potential cutaneous long-term side effects) [7].

Azoles are known to inhibit the 1α-hydroxylase and therefore decrease 1,25(OH)_2_D levels. These antifungal drugs are commonly used in neonates, infants, and adults; pharmacokinetic data are well described. In the early 2010s, ketoconazole was reported to decrease calciuria in patients with vitamin D hypersensitivity [8, 9]. However, its off-label use may be challenging, mainly because of its potential liver toxicity on the long term [10]. More recently, to improve azole tolerance, fluconazole has been successfully reported to reduce urinary calcium in a few patients with *CYP24A1* or *SLC34A3* mutations, while maintaining a stable renal function [3, 11].

Based on these observations, we hypothesize that fluconazole is effective to decrease and normalize calciuria in patients with hypercalciuria and increased 1,25(OH)_2_D levels. We will therefore conduct a placebo-controlled double-blind trial testing fluconazole in hypercalciuric patients with increased 1,25(OH)_2_D levels.

## Methods/design

The FLUCOLITH trial is a phase 2, prospective, interventional, national, randomized in parallel groups (1:1), placebo-controlled, exploratory double-blind trial, as summarized in Fig. 1.

**Fig. 1 Fig1:**
[figure not shown]
Overall summary of the FLUCOLITH trial

The national French recruitment will be ensured through two national rare disease networks (OSCAR and ORKiD networks); the participation of 26 French University Hospitals is expected, with physicians from Nephrology and Endocrinology Departments, and from adult and pediatric units (cf. Additional file 2 - List of study sites). The trial is supported by a grant from the French Ministry of Health (*Programme Hospitalier de Recherche Clinique National* 2019) and the study sponsor is the Hospices Civils de Lyon (Lyon, France). The funding body and the study sponsor are not involved in the design of the study and collection, analysis and interpretation of data, and the writing the protocol.

### Participants

#### Eligibility criteria

The inclusion criteria will be the following: patients who presented in their medical history nephrolithiasis and/or nephrocalcinosis; patients who had, at least 4 weeks (±2 weeks) before inclusion and at inclusion (V_1_), a local biological evaluation with 24-h urine calcium above 0.1 mmol/kg/day, and 1,25(OH)_2_D levels above or equal to 150 pmol/L, and 25-OH-D levels above or equal to 20 nmol/L, and calcemia levels below or equal to 2.65 mmol/L; children from 10 years or adults until 60 years; women using effective methods of contraception during the study period, partners of male patients of child-bearing potential must use highly effective methods of contraception; patients insured or beneficiary of a health insurance plan; evidence of signed and dated informed consent document(s) indicating that the subject and/or his parents/legal guardian have/has been informed of all pertinent aspects of the trial.

The non-inclusion criteria will be the following: patient who already received fluconazole or ketoconazole during the last 6 months before inclusion; patients weight below 28 kg; patients with BMI>35; patients who cannot stop hydrochlorothiazide or other diuretics during the screening and study period; patients who cannot stop vitamin D supplementation and/or calcium supplementation (drugs, enriched waters, etc.) during the study period; hypersensitivity to fluconazole and/or other derivative azoles and/or excipients; due to the presence of lactose excipient, patients presenting rare hereditary abnormalities of galactose intolerance, of Lapp lactase deficit, or of glucose-galactose malabsorption; patients who need co-administration with other drugs known to prolong the QT interval and metabolized by cytochrome P450 (CYP3A4) such as pimozide, quinidine, and erythromycin; patients with iatrogenic hypercalciuria (vitamin D intoxication, immobilization); patients with risk of QT interval prolongation (congenital Long QT syndrome, familial history of sudden cardiac death before 50 years of age, cardiopathy: ischemia or myocardial infarction, congestive cardiac insufficiency, left ventricle hypertrophy, cardiomyopathy, conduction trouble within 6 months preceding the inclusion, arrhythmia history, electrolytic instabilities; bradycardia (< 50 beats per minute), acute neurological events within 6 months preceding the inclusion, adult patients with a QT interval/corrected QT interval > 470 ms for women and > 450 ms for men at the ECG performed at the inclusion visit (V_1_), or children from 10 years with a QT interval/corrected QT interval should be > 460 ms for girls and > 450 ms for boys); children with a history of cardiac pathology, patients with an estimated glomerular filtration rate < 60 mL/min/1.73 m^2^; patients with a liver disease or an abnormality in the initial liver lab test; patients with enuresis; patients with another cause of identified nephrolithiasis; patients suffering from granulomatosis pathology such as sarcoidosis; patients with hyperparathyroidism; women who are pregnant or breast feeding, or who have a project of pregnancy before the end of the study; women menopaused; patients with a project of travelling in a sunny area during the study period; immunodeficient patients, patients with other diseases or disorders that could preclude assessment; patients who are participating in another research study that may interfere with the results or conclusions of this study; and patients under judicial protection.

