
### Intervention

The patients likely to participate in the study will be identified within the Nephrology and the Endocrinology Departments of the participating CHU, as part of their regular medical follow-up. Inclusions will be performed only from mid-September to the beginning of February so as to avoid bias due to sunlight-induced vitamin D synthesis.

Patients will receive fluconazole or placebo during 18 weeks.

A therapeutic adjustment will be done during the first 6 weeks of treatment (titration period) according to the 24-h calciuria results. Treatment will be modified if necessary by increasing the number of capsules. Treatment will start with 50 mg/day until maximum 200 mg/day. Patients allocated will receive between 1 and 4 capsules of fluconazole/placebo during the first 6 weeks of the trial.

The site personnel will directly enter calciuria results onto the eCRF. During the titration period (week 2 (V_3_), week 4 (V_4_), and week 6 (V_5_)), the posology to adopt will be automatically given by the eCRF, via an algorithm common to both treatment groups:If 24-h calciuria is > 0.1mmol/kg/day, fluconazole/placebo dose will be increased to 50 mg per day until the next visit,If 24-h calciuria is ≤ 0.1mmol/kg/day, fluconazole/placebo dose will remain stable until the next visit.

From week 6 (V_5_) and until the end of the treatment period (week 18, V_9_), the treatment dose will remain stable (stable period), as illustrated in Fig. 1.

Temporary or permanent discontinuation of investigational medical product can occur due to biological lab abnormalities (calcemia levels > 2.65 mmol/L after two tests, hepatic toxicity, neutrophil counts < 1000 cells/μL, platelet count < 150,000 cells/μL), all anaphylactic reaction, cardiac abnormalities observed on the ECG exam, renal insufficiency with creatinine clearance <50 mL/min/1.73 m^2^, significant vitamin D level reduction (25-OH-D level <20nmol/L), or hypophosphatemia.

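### The eligibility criteria ask a weaker contraception standard of women who may take fluconazole than of male patients' partners, who take no study drug

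*Protocol article*

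**What the plan says.** Contraception appears once in the protocol article, in the inclusion criteria under Eligibility criteria. One clause sets the condition for women in the trial and then the rule for the partners of men in the trial: "women using effective methods of contraception during the study period, partners of male patients of child-bearing potential must use highly effective methods of contraception".

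The non-inclusion criteria in the same section add "women who are pregnant or breast feeding, or who have a project of pregnancy before the end of the study", followed by "women menopaused" as a further reason for non-inclusion.

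Exposure is set out under Intervention: "Patients will receive fluconazole or placebo during 18 weeks", and "Treatment will start with 50 mg/day until maximum 200 mg/day". The dose is adjusted at weeks 2, 4 and 6 and then held to week 18. Partners of male patients are not trial patients and receive no capsules.

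**The concern.** The two terms are ranked by their wording: *highly effective* is stricter than *effective*. The stricter term is attached to the group that does not take the drug, and the weaker one to the group that may take it daily for 18 weeks. One would expect the reverse, or at least equal standards.

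The plan itself treats pregnancy during the study as something to avoid, since it does not include women who are pregnant or intend to become so. It also does not include menopausal women, so most adult women who enter can be expected to be of child-bearing potential, and the contraception rule will matter for most of them. What is at stake is the protection of participants against an unplanned pregnancy on study treatment. The trial's inference is not at stake.

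**Working it through.** There is no stated figure on this point to reproduce. The check is a comparison of the text, with simple arithmetic on exposure.

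**The two groups side by side**

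| | Female participants | Partners of male patients |
|---|---|---|
| Contraception standard (Eligibility criteria) | effective | highly effective |
| Study drug taken (Intervention) | fluconazole or placebo, 18 weeks | none |
| Fluconazole dose if so allocated | 50 to 200 mg/day | 0 |
| Pregnant, breast feeding or planning pregnancy (Eligibility criteria) | not included | no rule stated |

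**Does anything else close the gap?** The non-inclusion criteria deal with a pregnancy that exists at entry and with one that is intended. Neither condition prevents an unintended pregnancy after entry; for that, contraception is the only safeguard the article states. No other section mentions contraception, defines either term or raises the standard for women in the trial. The Benefit/risk ratio section does not mention pregnancy and gives no reason for the difference.

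**Exposure of a woman on fluconazole who completes treatment**

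Inputs, from Intervention: 18 weeks; 50 mg capsules, 1 to 4 per day; dose decisions at weeks 2, 4 and 6. Assumptions: steps of +50 mg, full adherence, no discontinuation.

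- Duration: 18 × 7 = 126 days.
- Minimum, never raised: 126 × 50 mg = 6,300 mg = 6.3 g.
- Maximum, raised at every decision: 14 × 50 + 14 × 100 + 14 × 150 + 84 × 200 = 700 + 1,400 + 2,100 + 16,800 = 21,000 mg = 21.0 g.
- Partner of a male patient: 0 g.

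**Number of women concerned**

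Input, from Sample size: 25 patients per group. The sex split is not given, so a female share of 30% to 70% is assumed.

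- 25 × 0.30 = 7.5, about 8.
- 25 × 0.70 = 17.5, about 18.

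This is an upper count of those at risk of pregnancy within the assumed range, because enrolment starts at age 10. As many again would be under the same standard on placebo.

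**Effect on the statistics.** None. The stated 89% power (15% versus 60%, 25 per group, two-sided 5% Fisher test) reproduces by exact enumeration at 0.892, and it does not depend on the contraception wording.

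**The case against.** The strongest reply is that this rests on one adverb in a condensed list. The article defines neither term, and lists of acceptable methods are normally left to the full protocol. The clause is loosely written: it joins two rules with a comma and places its modifier awkwardly. The difference may therefore be a slip of condensing or translation and not a deliberate design choice. It is also fair to say that the article states no reproductive risk of fluconazole, so the documents alone do not show that *effective* is inadequate. On that view the mismatch could equally be removed by relaxing the partner rule. Female participants are moreover covered by other entry conditions and by repeated study visits, whereas partners have only the one rule. Finally, grams of drug do not measure a difference in pregnancy risk.

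Some of this stands. The documents do not show whether the difference is intended, the gap in risk cannot be sized, and the exposure figures describe only who is exposed and by how much. The central point remains. The article does not merely omit a definition; it prints two ranked standards and assigns the lower one to the women with direct exposure. Definitions elsewhere would help only if they made the two terms equal or reversed them, and then this text would still need correcting. A reason to be strict with partners could not justify asking less of women who take the drug themselves. The additional conditions on participants do not address an unplanned pregnancy.

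**Conclusion.** The concern holds. As written, the criterion asks less of the women who may take 6.3 g to 21.0 g of fluconazole over 126 days than of women who take none, and nothing in the article explains or offsets this. Under the assumed female share of 30% to 70%, about 8 to 18 of 25 fluconazole patients fall under the lower standard.

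The conclusion rests on reading the two terms in their plain order and does not depend on the assumed sex split. It makes no claim about the actual difference in pregnancy risk, and none about the drug's effect in pregnancy. It is a participant-safety correction that should be made, held with medium confidence because the full protocol may word the rule differently.

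**What to change.** Amend the inclusion criterion so that female participants of child-bearing potential must use highly effective methods of contraception during the study period. This raises them to the standard the protocol already sets for partners of male patients; the partner rule can stay as it is. If the full protocol already sets one standard for both groups, correcting the article's wording is enough.

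The text change is one phrase. If it counts as a substantial modification, the Ethics section requires a favourable ethics committee opinion and authorization from the competent authority, followed by notification of the centers, of which 26 are expected. Under Trial status, recruitment was open at publication, with inclusions from January 2021 over an estimated 36 months, so later entrants could still benefit. The downside is that a few women may have to change method before entry. Sample size and analysis do not change.

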
### Intervention

The patients likely to participate in the study will be identified within the Nephrology and the Endocrinology Departments of the participating CHU, as part of their regular medical follow-up. Inclusions will be performed only from mid-September to the beginning of February so as to avoid bias due to sunlight-induced vitamin D synthesis.

Patients will receive fluconazole or placebo during 18 weeks.

A therapeutic adjustment will be done during the first 6 weeks of treatment (titration period) according to the 24-h calciuria results. Treatment will be modified if necessary by increasing the number of capsules. Treatment will start with 50 mg/day until maximum 200 mg/day. Patients allocated will receive between 1 and 4 capsules of fluconazole/placebo during the first 6 weeks of the trial.

The site personnel will directly enter calciuria results onto the eCRF. During the titration period (week 2 (V_3_), week 4 (V_4_), and week 6 (V_5_)), the posology to adopt will be automatically given by the eCRF, via an algorithm common to both treatment groups:If 24-h calciuria is > 0.1mmol/kg/day, fluconazole/placebo dose will be increased to 50 mg per day until the next visit,If 24-h calciuria is ≤ 0.1mmol/kg/day, fluconazole/placebo dose will remain stable until the next visit.

From week 6 (V_5_) and until the end of the treatment period (week 18, V_9_), the treatment dose will remain stable (stable period), as illustrated in Fig. 1.

Temporary or permanent discontinuation of investigational medical product can occur due to biological lab abnormalities (calcemia levels > 2.65 mmol/L after two tests, hepatic toxicity, neutrophil counts < 1000 cells/μL, platelet count < 150,000 cells/μL), all anaphylactic reaction, cardiac abnormalities observed on the ECG exam, renal insufficiency with creatinine clearance <50 mL/min/1.73 m^2^, significant vitamin D level reduction (25-OH-D level <20nmol/L), or hypophosphatemia.

Blinding procedure will be systematic thanks to the indistinguishable nature of the active product and placebo and their packaging. Participant, care provider, investigator, outcomes assessor, and the coordinating center are blinded to the arm of treatment. Since patients (and their representatives if applicable) and investigators are blinded to the treatment arm, this is referred to as a double-blind study even if all other participants are also blinded. Only the biostatistician in charge of the production of the randomization list, the Centre Anti-Poison of Lyon, and the main pharmacy (Pharmacy Department Groupement Hospitalier Centre – Edouard Herriot Hospital – Hospices Civils de Lyon (Lyon, France), responsible for packaging, labelling, and dispatching of experimental drugs to the sites will have access to a decoded list. Unblinding will be possible 24 h/7 days simply by phone call to the Centre Anti-Poison de Lyon (CAP - [name]). The CAP physician will be able to proceed to the unblinding if required.

The examinations realized during the visits will be performed specifically for the study: urine, and blood analysis, electrocardiogram, dual X-ray absorptiometry (DXA), renal ultrasounds, dietetic questionnaires, oral calcium load tests [12]. Bone evaluation will be done with DXA: femoral neck (FN), lumbar spine vertebra 2 to 4 (LS2-4), and total body (TB) areal bone mineral density (aBMD, g cm^−2^). For *Z*-scores for TB and LS2-4, aBMD will be calculated depending of age and gender. DXA will be performed locally and we will only keep the results as Z-scores from the different centers, provided that DXA scans are locally performed according to the ISCD (International Society of Clinical Densitometry) guidelines. All DXA images will be anonymized by the investigator sites and centralized on an internet platform. The investigators will only have an access to their patients. A central review of all DXA results will be done by an engineer from INSERM Unit 1033 “pathophysiology, diagnosis and treatment of musculoskeletal disorders” in Edouard Herriot Hospital in Lyon.

The investigational medicinal product (IMP) is fluconazole. For the study, the IMP and its placebo will be provided in 22 capsule numbered bottles. Placebo will be used as treatment of comparison as there is no gold standard strategy.

Fluconazole 50 mg and placebo capsules are provided, in the same appearance (color, size, and packaging) by the sponsor. The IMP and placebo are prepared, blinded, labelled, and delivered in every participating center by the Pharmacy of the Edouard Herriot Hospital (FRIPHARM, Hospices Civils Lyon, France), authorized for the compounding of experimental drugs. Preparation of the IMP is realized according to good preparation practices from tablets of Fluconazole ARROW® 50 mg, supplied by ARROW (France). The placebo capsules are composed of lactose (excipients in the labelling and package leaflet of medicinal products for human use).

Co-administration with medicinal products known to prolong the QT interval and metabolized by cytochrome P450 (CYP) 3A4 is contraindicated in patients treated with fluconazole. Halofantrine, Amiodarone, and medications used to treat the pathology are not recommended too.

